*In vivo* electroporation with the TriGridTM delivery system by Ichor Medical Systems, Inc. significantly enhances the cellular and humoral immunogenicity of DNA vaccines in animals, and has entered human clinical testing in cancer patients. This trial will investigate whether delivery of ADVAX by electroporation enhances either humoral or cellular immunogenicity in healthy volunteers. An enhanced immune response in the setting of electroporation could provide the proof-of-concept that DNA vaccines may act as stand alone vaccines against HIV or other diseases.

**Rational of Study, Research Plan and Procedures:**

This study is a Phase I, placebo controlled clinical trial to evaluate the administration of an HIV-1 vaccine encoding the *gag, env, pol, nef,* and *tat* antigens (ADVAX) in healthy volunteers by either *in vivo* electroporation or conventional intramuscular injection. The objectives of the study are to characterize the safety and tolerability of electroporation-mediated intramuscular delivery using the TriGridTM device by Ichor Medical Systems, Inc. and to compare the resulting antigen-specific immune responses to those elicited by conventional intramuscular injection of the vaccine. Safety of the vaccine delivered by electroporation will be characterized by documenting the nature, frequency, and severity of any toxicity associated with vaccination of ADVAX delivered by electroporation. Tolerability of the procedure will be assessed through the use of a brief questionnaire provided to the participants. Characterization of the immunogenicity of ADVAX delivered by electroporation or conventional intramuscular injection will include measurement of antigen-specific cellular and humoral immune responses. Recent data from ADVAX administered IM versus EP in Balb-C mice suggests that three vaccinations by EP elicit superior humoral and cellular immunogenicity than two vaccinations by EP. Two vaccinations have been safe and tolerable in all dose groups in humans to date. We have therefore secured enough vaccine to provide one additional vaccination to the high dose EP group at Week 36. This will allow participants in the high dose group who have been randomized to receive EP (either ADVAX or placebo) to elect to receive three vaccinations on a voluntary basis in order to maximize potential immunogenicity.

Study Procedures:

**Pre-Screening Questionnaire**

Potential participants will first undergo pre-screening by telephone to assess medical history and qualification for the study. They will have the opportunity to discuss the study and ask questions of the study recruiter at this time. Those who are eligible and interested in participation will attend a screening visit at the Rockefeller Hospital Outpatient Clinic. This is the same procedure that was conducted for the ADVAX (DHO-519) and ADMVA (DHO-549) trials.

**Screening Visit**

During the screening visit, study personnel will answer any questions about the study. Written site-specific informed consent will be obtained prior to conducting any study procedures. To ensure informed consent, the principal investigator or designee will discuss the following processes and explanations individually with each volunteer:

1. Pre HIV-test counseling
2. Risk-reduction counseling including safe-sex counseling
3. That it is unknown whether or not the study vaccine will protect against HIV infection or disease and, if so, the extent of that protection
4. That, following vaccination, it may be possible that the volunteer will develop antibodies against HIV, which may produce a positive reaction in a routine HIV test, and that provisions have been made to distinguish between response to vaccine and HIV infection during and after the trial
5. That a sexually active volunteer should use a reliable form of contraception from screening until end of study
6. Describe the electroporation procedure, including measurement of skin-fold thickness, both verbally and with a video.

If the volunteer consents to participate, site personnel will:

- Perform HIV risk assessment
- Perform complete medical history (including concomitant medication)
- Perform a general physical examination including height, weight, vital signs (pulse, respiratory rate, blood pressure and temperature), examination of skin, respiratory, cardiovascular and abdominal systems, and an assessment of cervical and axillary lymph nodes
- Perform a skin-fold measurement of the upper arm (Appendix B)
- Collect blood and urine specimens for all tests as indicated in the Schedule of Procedures (Appendix A)
- Perform a pregnancy test for all female volunteers

Screening laboratory test(s) may be repeated once at the discretion of the principal investigator or designee to investigate any isolated abnormalities.

If the screening visit occurs more than 42 days prior to date of vaccination, then study procedures for the screening visit must be repeated. However, the complete medical history may be replaced by an interim medical history and the informed consent form may be reviewed without signing again.

**Vaccination Visits (Day 0 and Week 8; and Week 36 for high dose volunteers in the EP group who elect to receive a third vaccination)**

Prior to the vaccination, site personnel will:

- Answer any questions about the study
- Review interim medical history (including concomitant medications)
- Review safety laboratory data
- Review the informed consent form administered at screening visit with volunteer
- Perform a directed physical examination including vital signs (pulse, respiratory rate, blood pressure and temperature) as well as an assessment of axillary lymph nodes and any further examination indicated by history or observation
- Conduct pre HIV-test counseling
- Perform a skin-fold measurement of the upper arm (Appendix B)
- Collect blood and urine specimens for all tests as indicated in the Schedule of Procedures (Appendix A)
- Perform a pregnancy test for all female volunteers (blood will be sent stat)and obtain results prior to vaccination
- Perform baseline assessment of the site of injection and evaluate and record any systemic symptoms
- Administer vaccine (the preferred site of administration is the deltoid muscle of the upper arm) either by standard intramuscular injection or by electroporation. Depending upon the amount of adipose tissue at injection site, the length and gauge of the standard intramuscular needle and the gauge of the electroporation device will be adjusted (Appendix B)

Volunteers will be closely observed for at least 30 – 45 minutes after vaccination. Vital signs (pulse, respiratory rate, blood pressure and temperature) will be monitored at 30 – 45 minutes after vaccination and recorded. Any local and systemic reactogenicity events, as well as any other event that occurs, will be recorded at 30 – 45 minutes. At this time, subjects will also be asked to complete a Vaccine Tolerability Assessment Form (Appendix D). Furthermore, volunteers will be given a diary card (Appendix E) and asked to record any reactogenicity events that occur between Day 1 and Day 7 and Day 57 and Day 64, as well as Day 253 and Day 260 in those volunteers in the high dose EP group who elect to receive a third vaccination. Site staff will explain to the volunteer how to record reactogenicity events.

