### Human trials with DNA vaccines

Several studies have been performed in humans with DNA vaccines other than HIV.DNA vaccines. Anti-malaria DNA vaccines administered intramuscularly induced some CTL and no antibody responses, and were well tolerated up to 2.5 mg per dose.15,16 A pilot study (Protocol 400-003-03) with an HIV env/rev DNA construct was conducted in HIV-uninfected volunteers at the National Institutes of Health (NIH) Clinical Centre, USA. Doses as high as 3 mg were given as a single injection. Adverse events were mild and infrequent and T-cell responses were observed.17

A Phase 1 clinical study (AVEG Protocol 031) with an HIV-1 gag/pol DNA vaccine was performed in 52 HIV-1 uninfected adult volunteers aged 18-60 years with low risk for HIV-1 infection. Doses as high as 3 mg at 0, 1, 3 and 6 months were given. This vaccine was able to induce antigen-specific proliferation and production of chemokines by PBMC of vaccinated individuals, *in vitro*. Preliminary data on this HIV-1 gag-pol DNA vaccine were presented by Tellez et al. 18

In early 2000, Merck began a human trial of a DNA vaccine using HIV gag with the intention to boost with recombinant adenovirus. Preliminary data have been presented documenting safety and immunogenicity (Emini, CROI IX, Seattle, Washington, 2002).

A candidate DNA.HIVA vaccine has undergone Phase 1 clinical trials through the collaboration of IAVI, the Medical Research Council in Oxford, UK and with the Kenya Aids Vaccine Initiative (KAVI) in Nairobi, Kenya. The DNA.HIVA vaccine was given to a total of 31 volunteers at either 100µg (n=6) or 500 µg (n=25) intramuscularly. It has been well tolerated and immunogenic. Local side effects observed in the UK trial were mild to moderate, occurred mostly on the first post-vaccination day and resolved by 48 hours. Systemic side effects were mild to moderate and resolved within 1-3 days. In the Kenya trial no local or systemic side effects have been observed. A Phase 1 study testing a prime-boost approach and enrolling 120 volunteers started at the beginning of April 2002 in the UK. Dosage levels up to 2 mg DNA. HIVA per injection are being tested. As of May 19, 2003, approximately 103 individuals have been enrolled. No pattern of risk has been found among reported events. Thus far the vaccine has been found to be generally safe and well tolerated.

Human Trials with ADARC Vaccines

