**Priming**

**Vaccination**

**Week 0**

**Week 36**

**Boosting**

**Vaccination**

**Week 56**

**Study**

**Conclusion**

**Priming**

**Optional Boosting**

**Vaccination**

**Study**

**Week 8**

**Follow-up**

**Administration Procedure**

ADVAX or placebo will be administered intramuscularly to the deltoid muscle. Subjects will be administered the study drug using Ichor Medical Systems’ intramuscular TriGrid delivery device. The Ichor device will be used only by personnel who have completed Ichor’s training seminar. The seminar will be conducted by Ichor personnel and will require approximately 60-90 minutes to complete. Topics will include setup and operation of the equipment, procedures for administration of the DNA vaccine, troubleshooting, and device care and storage. Each participant must successfully complete at least three mock administration procedures demonstrate competency.

Vials will be thawed at room temperature on the day of study visits. Immediately upon thawing and mixing of the vaccine vials, study vaccine/placebo will be withdrawn into 3.0 cc Becton Dickinson Model 309585 syringes under sterile conditions by the research pharmacist. Any unused portion of vials and syringes will be disposed of in accordance with Rockefeller University Pharmacy policy.

ADVAX will be administered as a single injection at the Day 0 and Week 8 time points, and for those volunteers in the high dose EP cohort who elect to receive a third vaccination, again at Week 36. The first and second vaccination will be given in alternating arms, and any optional third vaccinations will be given in the arm where the first vaccination was administered. Under no circumstances will the study vaccine/placebo be administered to regions of tissue that do not have intact lymph drainage. All subjects will be observed in clinic for a minimum of 30-45 minutes following each vaccination. Subjects receiving electroporation will complete a Tolerability Assessment Form (Appendix B).

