**APPENDIX D: Volunteer Diary Card**

**Volunteer Diary Card**

**Protocol DHO-0614-0707**

Volunteer ID Number

Date and time of injection

Date of Next Visit:

Name of Study Contact:

24 HOUR EMERGENCY telephone number to report any unusual or severe symptoms that occur before the next visit:

** Please bring this card to your next clinic visit.

If you experience any symptoms following this vaccination that persist beyond day 3 (72 hours) please indicate the severity for each one noted in the column under the day you noticed the symptom. Unless an item says MEASURE, please rate severity as “-“for none, “+” for mild, “++” for moderate, or “+++” for severe.

| **Code** | **Meaning** |
| --- | --- |
| - | Symptom not present |
| + | Mild: Transient or mild discomfort, no limitation in normal daily activity |
| ++ | Moderate: Some limitation in normal daily activity |
| +++ | Severe: Unable to perform normal daily activity |

| **Possible Symptoms** | **Date** | **Date** | **Date** | **Date** | **Date** | **Date** | **Date** |
| --- | --- | --- | --- | --- | --- | --- | --- |
| Local Symptoms  Pain (pain without area being touched) at injection site |  |  |  |  |  |  |  |
| Tenderness (pain when area being touched) at injection site |  |  |  |  |  |  |  |
| Redness (erythema) at injection site  MEASURE | mm | mm | mm | mm | mm | mm | mm |
| Skin damage (vesicles, ulcers) at injection site  MEASURE | mm | mm | mm | mm | mm | mm | mm |
| Hardness or thickening (induration) at injection site MEASURE | mm | mm | mm | mm | mm | mm | mm |
| Swelling (edema) at injection site |  |  |  |  |  |  |  |
| Formation of crust, scab or scar MEASURE | mm | mm | mm | mm | mm | mm | mm |
| Systemic Symptoms  Headache |  |  |  |  |  |  |  |
| Chills |  |  |  |  |  |  |  |
| Nausea |  |  |  |  |  |  |  |
| Vomiting |  |  |  |  |  |  |  |
| Temperature MEASURE  Measure before midnight of the date stated | °F | °F | °F | °F | °F | °F | °F |
| Feeling of general discomfort, uneasiness, a general sick feeling (malaise) |  |  |  |  |  |  |  |
| Muscle aches (myalgia) |  |  |  |  |  |  |  |
| Aching joints (arthralgia) |  |  |  |  |  |  |  |

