**How to Measure Thickening and Redness and skin damage**

Check for hardness or thickening (induration), redness (erythema) and skin damage (vesicles, ulcers) at injection site on Day 1, 2 and 3 after each injection. (Day 1, 2 and 3 are 24, 48, and 72 hours after study vaccination respectively).

If you see any thickening, redness, or lump at the injection site, use the measuring tape provided to measure the WIDEST part of the response on Days 1, 2, and 3.

Record the result rounded to the *nearest 10*, for example, 0, 10, 20, or 30.

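### The diary starts the day after each dose, so the evening of vaccination has no self-record, and its window is 7 days after dose 1 but 8 days after doses 2 and 3

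*Protocol*

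**What the plan says.** Under Administration Procedure, "ADVAX will be administered as a single injection at the Day 0 and Week 8 time points", with an optional third dose at Week 36 for high-dose electroporation (EP) volunteers.

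On the vaccination day the Vaccination Visits section requires a staff record: "Any local and systemic reactogenicity events, as well as any other event that occurs, will be recorded at 30 – 45 minutes". Vital signs, including temperature, are taken at the same time, and the volunteer fills in a tolerability form. The volunteer then takes home a diary card and is "asked to record any reactogenicity events that occur between Day 1 and Day 7 and Day 57 and Day 64", with Days 253 to 260 for a third dose.

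The diary card appendix tells the volunteer: "Please bring this card to your next clinic visit". It has seven columns, each headed only with a date. Its measuring instructions state: "Day 1, 2 and 3 are 24, 48, and 72 hours after study vaccination respectively". The oral temperature directions supply thermometers for those same three days.

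Section d, Primary Endpoints, includes severe local and systemic reactions and the proportion of volunteers with mild and moderate ones. Post-Vaccination Visits adds a telephone call 1 to 4 days after each dose and clinic assessments 1, 2 and 4 weeks after it.

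**The concern.** Reactions to an injection or to electroporation can begin within hours and settle overnight. In its background the protocol reports that local effects of another intramuscular DNA vaccine "occurred mostly on the first post-vaccination day and resolved by 48 hours". That phrase fits either the day of dosing or the day after, so it does not show that reactions vanish before the diary opens. It does show that early, short reactions are to be expected.

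A reaction confined to the evening of vaccination is recorded only if the volunteer mentions it at a later call or visit. The opportunity for early recall is also unequal. The additional day-after call goes only to the first four EP recipients in each dose group, and to no volunteer given a conventional injection. A diary entry on the evening of dosing would be the same for everyone.

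A window that is one day longer after the second and third doses also means that per-dose reaction rates do not cover equal periods.

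**Working it through.** **Inputs**
- Dose days: Day 0; Week 8 = 8 × 7 = Day 56; Week 36 = 36 × 7 = Day 252. The Appendix A phone days agree: 59 = 56 + 3 and 255 = 252 + 3, matching the Day 3 call after dose 1. One line under Post-Vaccination Visits places the third dose at Week 38. Week 36 is used here because the diary days and Appendix A are counted from it.
- Diary windows (Vaccination Visits): Days 1–7, 57–64, 253–260.
- Next clinic visit (Appendix A): Weeks 1, 9, 37 = Days 7, 63, 259, with a 2-day window. The sign is not legible in the text; plus or minus 2 is assumed.
- Card: seven date columns.

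**Start of the diary.** First diary day minus dose day: 1 − 0 = 57 − 56 = 253 − 252 = 1 day. The length of the gap depends on what a diary day is:
- If Day 1 is the 24-hour point, the gap runs from the clinic check to 24 hours: 24 − 0.75 = 23.25 h to 24 − 0.5 = 23.5 h.
- If a diary day is a calendar date, as the temperature row implies ("Measure before midnight of the date stated"), the gap runs from the clinic check to midnight. Its length depends on the hour of dosing, which is not stated.

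On either reading no entry is requested for the evening of vaccination.

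**Length of the window.** Last − first + 1: 7 − 1 + 1 = 7; 64 − 57 + 1 = 8; 260 − 253 + 1 = 8. With seven columns, 8 − 7 = 1 diary day after doses 2 and 3 has no column.

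**Return of the card.** With calendar days, days incomplete at the visit = max(0, last day − visit day + 1).

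| | Dose 1 | Dose 2 | Dose 3 |
| --- | --- | --- | --- |
| Last diary day | 7 | 64 | 260 |
| Nominal visit | 7 | 63 | 259 |
| Last day − nominal visit | 0 | 1 | 1 |
| Incomplete, visit on time | 1 | 2 | 2 |
| Incomplete, visit 2 days early | 3 | 4 | 4 |
| Incomplete, visit 2 days late | 0 | 0 | 0 |

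With 24-hour points the on-time shortfall is the third row: 0, 1 and 1. So an on-time shortfall after dose 1 exists only under the calendar reading, while one of at least a day after doses 2 and 3 exists under both.

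**What recall can restore.** Appendix C grades malaise, headache and pain by their effect on activity, which a volunteer can describe later. It grades fever by measured temperature (mild starts at 37.7 °C) and induration by diameter. After the 30–45 minute check the next requested reading is on Day 1. A fever that rises and settles before then has no reading and cannot be graded.

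**Scale.** With 8 volunteers per group, each one misclassified moves a proportion by 1/8 = 12.5 percentage points. This is the size of one step, not an estimate of how many are missed.

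**The case against.** Several arguments limit this point.

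- A reader might infer that vaccination-day reactions have no prospective record. They have one: the staff record, vital signs and tolerability form at 30–45 minutes. Only the hours after that are uncovered.
- A reader might pair the gap of about 23 hours with an incomplete last day after dose 1. The first uses 24-hour points and the second uses calendar dates, so both cannot hold for an on-time visit.
- A reader might infer that the card is surrendered early. The text says only that it is brought; a visit two days late covers the whole window, and later visits still assess reactogenicity.
- A reader might convert the gap into a bias. If 10–40% of reactions began and ended before the first entry, a true 4/8 (50%) would appear on the diary as 45% to 30%. The documents do not supply that share, and the endpoint is not defined by the diary alone, because calls and visits also feed it. Nor do they say that overnight reactions are those that best separate EP from conventional injection.
- The card does not forbid using its first column for the dosing date. That is true, but seven columns starting on Day 0 would end on Day 6, and the Vaccination Visits text and thermometer directions would still start at Day 1.
- The analysis is descriptive, and every arm uses the same card. This lowers the stakes but does not remove them, since reactogenicity is a primary endpoint.

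The card has a further conflict: it asks only for symptoms lasting beyond 72 hours, against any event in the Vaccination Visits text. That needs its own reconciliation, and correcting it would not change the start day or the window lengths.

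**Conclusion.** The point holds in a limited form. As written, the plan requests no self-recorded symptom, temperature or lesion entry between the clinic check and the day after each dose. Depending on the day convention, the gap is the rest of the vaccination day or 23.25 to 23.5 hours. Events in it depend on recall, and a brief fever cannot be recovered by recall.

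Separately, the windows contradict one another and the card: 7, 8 and 8 days against seven columns, with the last two ending one day after the nominal return visit.

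The day counts assume on-schedule doses and visits; the early and late cases also assume a plus or minus 2-day window. How many events are lost, and whether the loss differs by arm, cannot be determined from the documents. This should be corrected, but it does not undermine the design.

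**What to change.** In the Vaccination Visits text, the diary card, the measuring instructions and the oral temperature directions:

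1. Add a column for the evening of vaccination (Day 0) with symptoms, temperature and lesion measurement.
2. Use one window after every dose, Day 0 to Day 7: on schedule, Days 0–7, 56–63 and 252–259. That is 7 − 0 + 1 = 8 columns.
3. State whether a diary day is a calendar date or a 24-hour point, and use that meaning throughout.
4. State that a card whose last day is not complete at the Week 1, 9 or 37 visit is reviewed there and collected at the existing Week 2, 10 or 38 visit.

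The cost is one extra column, one more temperature reading per dose and slightly later collection of some cards. No visit is added. A card taken home again can be lost, so the entries made so far should be copied at the review.

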**Post-Vaccination Visits**

Volunteers will receive a phone call from the study staff between 1 and 4 days after each vaccination and volunteers will be asked to return to the clinic 1, 2 and 4 weeks after the first vaccination (given at Day 0) and at weeks 9, 10 and 12 after the second vaccination (given at Week 8), and for those volunteers in the high dose EP group who elect to receive a third vaccination (given at Week 38) at Weeks 37, 38, 40, and 44. At those visits, the following will be conducted:

- Review of interim medical history and use of concomitant medications
- If symptoms are present, perform a symptom-directed physical examination
- Assess local and systemic reactogenicity as well as any other adverse events (At Week 44 only adverse events will be assessed)
- Collect blood and urine specimens for all tests as indicated in the Schedule of Procedures (Appendix A)

